### Statistical analysis

2.6.

In this study, the baseline characteristics will be summarized as the mean ± standard deviation (SD) or median (interquartile range, IQR) for continuous data and(percentages) for categorical data. We will use the univariable and multivariable logistic regression analysis to evaluate some potential predictors for csPCa (i.e., PSA density, age, prostate volume). We will use student's *t*-test for continuous variables and chi-square or Fisher exact test for categorical variables to compare the difference between group A and group B. The statistical software package R (http://www.R-project.org, The R Foundation, Boston, Massachusetts, USA) and EmpowerStats (http://www.empowerstats.com, X & Y Solutions, Inc., Boston, MA) will be used to conduct statistical analyses. All results of the analysis are considered to be statistically significant with a two-sided *P* < 0.05.

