### Study design, randomization, and blinding

2.2.

Our protocol is a single-center, prospective RCT. Patients' demographic, clinical, and laboratory data will be obtained prospectively from electronic medical records of West China Hospital. We used a computer-generated random number to establish the randomization sequence. Eligible participants will be randomly allocated to either 6-core systematic plus 3-core MRI-TBx group (Group A) or 12-core systematic plus 3-core MRI-TBx group (Group B) with a ratio of 1:1 (Figure 1). In our trial, the urologist will not be blinded to any results because they will use the clinical and MRI findings to make clinical decisions and perform prostate biopsies.

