#### Outcome

2.4.2.

The primary outcome compares the detection rate of PCa and csPCa between group A and group B where csPCa is defined using the Gleason scoring system (Gleason ≥3 + 4) (11). The secondary outcomes conclude as follow: (1) The yield of clinically significant prostate cancer on each side of prostate comparing it to side of lesions (contra- or ipsilateral to lesions). (2) The PCa and csPCa detection rate when adding transitional zone cores (11 and 12 cores in total). (3) The PCa and csPCa detection rate between Group A and 10-core SB plus 3-core TB in Group B. (4) The PCa and csPCa detection rate between transitional zone and peripheral zone in Group A and Group B. (5) Comparing the participant-reported pain score immediate post biopsy using pain measurement scale (Supplementary Figure S1). (6) proportion of men with post-biopsy complications and adverse events (Time frame: 7 days post biopsy, 30 days post biopsy), which include pain, fever, urinary infection/prostatitis needing antibiotics, urinary retention, erectile dysfunction, urinary incontinence, haematochezia, haematuria, and haemotospermia. (7) proportion of the men who undergo radical prostatectomy and have cancer upgraded histopathology from the biopsy to the radical prostatectomy (Table 1).

**Table 1 T1:** Schedule of record.

	Visit 0	Visit 1	Visit 2	Visit 3
Weeks	−1	0	1	4
Teleconsult	×		×	×
Inclusion/Exclusion	×			
Family history of prostate cancer	×			
Informed consent	×			
Age	×			
t-PSA level	×			
free/total PSA ratio	×			
mpMRI result	×			
Number of lesions	×			
Size of lesions	×			
Index lesion PIRADS score	×			
Biopsy outcome			×	
Benign tissue			×	
Atypical small acinar proliferation			×	
High-grade prostatic intraepithelial neoplasia			×	
Clinically insignificant cancer			×	
Clinically significant cancer			×	
Positive biopsy cores			×	
Gleason score			×	
Men who did not undergo biopsy		×		
Undergo surgery				×
Surgery outcome				×
Pathology Gleason score				×
Immediate post biopsy questionnaire (pain)		×		
Complications		×	×	×

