### Sample size estimation

2.5.

We calculated sample size according to our results of retrospective database. Based on a power of 80% and a 2.5% one-sided *α*, we used an estimate for detection rate of PCa for 6-core systematic plus 3-core MRI-targeted prostate biopsy of 61.2% and an estimate of detection rate for 12-core systematic plus 3-core MRI-targeted prostate biopsy of 64.5%. Thus, 132 men per group will be required. Accounting for a dropout rate of 10%, 280 men will need to be recruited.

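### The only A-versus-B test named for detection is unadjusted, although PI-RADS, PSA and age are recorded before biopsy; a pre-specified adjusted risk difference would gain precision

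*Protocol article*

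**What the plan says.** - **Primary outcome (Outcome section):** "The primary outcome compares the detection rate of PCa and csPCa between group A and group B". Both endpoints are binary.
- **Between-group method (Statistical analysis):** categorical variables are compared between groups by chi-square or Fisher exact test. No adjusted estimate of the group effect is described.
- **Regression (same section):** a "univariable and multivariable logistic regression analysis to evaluate some potential predictors for csPCa (i.e., PSA density, age, prostate volume"). Neither randomised group nor PI-RADS is on that list.
- **Baseline data (Table 1, schedule of record):** "Index lesion PIRADS score" is recorded at Visit 0, as are age, total PSA and lesion size. Eligibility admits PI-RADS scores above 2, so the trial spans scores 3 to 5.
- **Randomisation (section 2.2):** "We used a computer-generated random number to establish the randomization sequence", at 1:1. No stratification factor is named.
- **Sample size (section 2.5):** "Based on a power of 80% and a 2.5% one-sided" alpha, with PCa detection assumed at 61.2% (6+3 cores) and 64.5% (12+3 cores), and the conclusion that "132 men per group will be required".

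**The concern.** The trial asks whether six fewer systematic cores can be accepted, so the width of the interval around the detection difference largely decides whether the result is usable. PI-RADS is a natural candidate for a strong prognostic factor for detection. An analysis that ignores a prognostic baseline variable leaves its variance in the error term. The plan already measures the variable and already uses logistic regression, but not for the randomised question. If the adjusted analysis is not fixed in advance, adopting it after the data are seen would be open to challenge.

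**Working it through.** **Inputs from the protocol article:** detection rates 0.612 and 0.645 (difference 0.033), 132 men per group, 80% power, one-sided alpha 2.5%.

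**1. The plan's own figure.**
- Variance sum = 0.612×0.388 + 0.645×0.355 = 0.4664.
- A superiority test of 0.033 needs 3,365 per group; power at 132 is about 8%.
- A non-inferiority calculation gives 132 only with a 20-point margin: (1.96 + 0.84)² × 0.4664 / (0.20 − 0.033)² ≈ 131.3, rounded up to 132. The article states no such margin. It is back-solved and used below only as a reference point.

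**2. Unadjusted precision.** SE = √(0.4664/132) = 0.0594, or 5.9 points. The 95% half-width is 1.96 × 5.94 = 11.7 points.

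**3. What PI-RADS adjustment would gain.** The documents give no PI-RADS distribution and no detection rate by score, so the shares and rates below are assumptions. Let B be the between-score variance of the detection rate and p the overall rate. Then R² = B / [p(1−p)]. Approximately, adjusted SE = unadjusted SE × √(1−R²), and effective n = 132/(1−R²).

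| Shares, PI-RADS 3/4/5 | PCa rates | p | B | R² | SE cut | Effective n per group |
|---|---|---|---|---|---|---|
| 30/45/25% | 45/65/85% | 64.0% | 0.0219 | 0.095 | 4.9% | 146 |
| 35/45/20% | 40/70/85% | 62.5% | 0.0304 | 0.130 | 6.7% | 152 |
| 30/45/25% | 30/72/90% | 63.9% | 0.0545 | 0.236 | 12.6% | 173 |
| 30/40/30% | 25/65/92% | 61.1% | 0.0683 | 0.288 | 15.6% | 185 |

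The half-width falls from 11.7 points to 11.1 in the first row and 9.8 in the last.

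**4. Sensitivity to the assumptions.**
- Weaker gradient: halving the distances from the mean in the first row divides B by four. R² becomes 0.095/4 = 0.024, the SE cut is 1 − √0.976 = 1.2%, and effective n is 132/0.976 = 135.
- Stronger gradient: shares 35/40/25% with rates 25/75/97% give R² = 0.366 and an effective gain of 58%.

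**5. Effect on power.**
- Superiority at 3.3 points: Φ(0.033/SE − 1.96). Unadjusted, SE 0.0594 gives 8.0%. Adjusted, SE 0.0565 to 0.0502 gives 8.4% to 9.6%.
- Back-solved 20-point margin: Φ(0.167/SE − 1.96). Unadjusted gives 80%; the same adjusted SEs give about 84% to 91%.

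**6. Chance imbalance.** Under simple 1:1 allocation, PI-RADS imbalance moves the raw difference with SD √(2B/132) = 1.8 to 3.2 points, so a shift beyond 3.3 points has probability about 7% to 31%. This variation is already inside the unadjusted SE. In the first row, 1.82² + 5.65² = 35.3, which equals 5.94². It is the share that adjustment removes, not an extra error.

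**The case against.** The strongest reply is that a chi-square test in a 1:1 randomised trial is a standard, valid choice. It keeps its type I error, the raw risk difference is unbiased, and the SE allows for chance imbalance. This stands, and it limits the point to efficiency.

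Three stronger readings are tempting, and the documents support none of them.

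- **That randomisation is unstratified.** Section 2.2 names no stratification factor but does not exclude one, and a condensed article may leave it out. If allocation was stratified by PI-RADS, the imbalance in step 6 largely disappears. The fix still applies, because an unadjusted test would then ignore a design factor.
- **That the regression is faulty because it omits allocation and PI-RADS.** It is an exploratory search for csPCa predictors and need not contain allocation. Its wording also leaves unclear whether the three listed variables are the full set.
- **That nothing protects the comparison from imbalance as large as the expected effect.** Randomisation and a correct SE do protect it. A 3.3-point shift is plausible mainly because 3.3 points is only 0.033/0.0594 = 0.56 of one SE, which is a sample-size matter.

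It can also be said that covariate adjustment is detail for an analysis plan that is not shown. That would answer a complaint about silence. Here the article does name the A-versus-B method, and a better one is available from data already scheduled.

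Finally, the size of the gain rests on assumed inputs. This also stands: the direction is secure, the amount is not.

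**Conclusion.** The point holds as a moderate efficiency improvement, not as an error of validity. With R² of about 0.10-0.29, a PI-RADS-adjusted risk difference would have an SE about 5-16% smaller, worth about 146-185 men per group instead of 132. The gain could be near 1% if detection varies little by score, and larger than 16% if it varies very steeply. These figures assume PI-RADS shares and detection rates that the documents do not give, and they count PI-RADS alone. They concern PCa; the article gives no csPCa rate to calculate from. Adjustment does not repair a superiority comparison of 3.3 points. The rise in power from 80% to about 84-91% applies only under the unstated 20-point margin.

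**What to change.** Pre-specify, before any outcome data are seen, that the primary estimate for PCa and for csPCa is the covariate-adjusted risk difference (A minus B) with a 95% CI:

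- Fit a logistic model with randomised group, index-lesion PI-RADS (3, 4, 5), log total PSA and age.
- Standardise the predicted risks over all randomised men analysed, and take the CI by delta method or bootstrap.
- Report the unadjusted difference and the chi-square or Fisher test as supportive.
- If allocation was stratified, state the factors and include them in the model.
- Keep the csPCa predictor regression as a separate exploratory analysis.

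The cost is a few lines of text and code, with no new data, visits or patients. For PCa, the model's five slope parameters are supported by about 132 × (0.388 + 0.355) = 98 men without cancer, the smaller outcome class, or roughly 20 per parameter.

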However, the optimal cores for the combined systematic and TBx have not been fully investigated. In the era of mpMRI, our previously study found that for suspected mpMRI lesions, the third targeted core can increase the detection rate of csPCa by 11.5% (13.5–26.7%) based on the first two cores; however, the incremental value of adding the fourth or the fifth core was only 6.0% (range: 4.7%–6.9%) and 4.1% respectively (8). Song et al. also supported that a 3-core TBx per lesion was suitable during transperineal MRI ultrasound fusion biopsy. It is worthy of note that currently the SBx still applied the traditional scheme of 10- to 12 cores while adding to the combined biopsy strategy, which might overlap the mpMRI lesions and lead to the unnecessary repeat biopsies. Using as few biopsy cores as possible is likely to reduce procedure time and pathologists' workload and minimize patient discomfort as well as the incidence of complications (9). Therefore, the clinical goal is to figure out how to determine the optimal systematic and TBx cores for the current combined approach, which can maximize the detection rate of csPCa while minimizing the associated defects, especially in the setting of transperineal biopsy under local anesthesia.

Thus, this prospectively randomized controlled trial (RCT) aims to explore the efficacy and safety of the new biopsy strategy combining 6-core systematic and 3-core MRI-TBx compared to 12-core systematic and 3-core MRI-TBx. We will indicate whether 6-core systematic plus 3-core MRI-targeted prostate biopsy could be performed, thus, decreased SBx cores in the detection of csPCa.

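### The only test stated for the primary outcome is a two-sided test of difference, which cannot show that 6+3 cores can replace 12+3; the sizing fits only non-inferiority, by inference

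*Protocol article*

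**What the plan says.** Section 2.4 (Outcome) makes the detection rates of PCa and csPCa, compared between Groups A and B, the primary outcome. Both are binary.

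Section 2.6 (Statistical analysis) gives a Student's t-test for continuous variables and a "chi-square or Fisher exact test for categorical variables to compare the difference between group A and group B". It adds: "All results of the analysis are considered to be statistically significant with a two-sided" P < 0.05. It gives no other between-group comparison for a binary outcome.

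Section 2.5 (Sample size estimation) opens with "Based on a power of 80% and a 2.5% one-sided" alpha. It assumes PCa detection of 61.2% in the 6+3-core arm and 64.5% in the 12+3-core arm, which gives 132 men per group, and 280 in total after an allowance for dropout. It names no hypothesis and no margin.

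The Introduction states the aim: "We will indicate whether 6-core systematic plus 3-core MRI-targeted prostate biopsy could be performed". The Conclusion (section 4) likewise asks whether fewer systematic cores can be used.

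**The concern.** The question is whether halving the systematic cores keeps detection acceptably close to that of the standard template, and the protocol itself expects slightly lower detection in the reduced arm. A chi-square or Fisher test has no difference as its null hypothesis. Rejecting it shows that the arms differ, which would either count against the new template or reveal an unexpected gain. Failing to reject it does not show that detection is preserved. Neither outcome of the stated test answers the question.

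At stake is the trial's main conclusion. If the test is all there is, nothing in the stated analysis limits the chance of endorsing a template that misses cancers the standard one would find.

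**Working it through.** **Inputs.** From section 2.5: pA = 0.612, pB = 0.645, difference 0.033, one-sided alpha 0.025, power 80%, n = 132 per group. From section 2.2: 1:1 allocation. The margin is not stated and is treated below as an assumption over a range.

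**1. Can 132 be reproduced as a test of difference?**

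n = [1.96·√(2·p̄·q̄) + 0.8416·√(pA·qA + pB·qB)]² / 0.033²

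- p̄ = 0.6285, so 2·p̄·q̄ = 0.4670
- pA·qA + pB·qB = 0.2375 + 0.2290 = 0.4664
- n = (1.3394 + 0.5748)² / 0.001089 ≈ 3,365 per group

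With a continuity correction n is 3,425, and at one-sided 5% it is 2,651. With 132 per group, the power to detect 64.5% against 61.2% is about 8%. The stated figure cannot come from a test of difference.

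**2. Can it be reproduced as non-inferiority?**

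n = (1.96 + 0.8416)² · 0.4664 / (margin − 0.033)²

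| Assumed margin | n per group for 80% power | Power with 132 per group |
|---|---|---|
| 10 points | 816 | about 20% |
| 15 points | 268 | about 50% |
| 20 points | 132 | about 80% |

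At 20 points: 7.849 × 0.4664 / 0.167² = 131.3, which rounds up to 132. Two other non-inferiority set-ups come close: no true difference with a 16.5-point margin, and the two rates reversed with a 13.3-point margin, each giving 133. Of the readings tried, only non-inferiority ones come near 132. The one that uses the stated rates as stated implies 20 points.

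**3. What does the stated test do at this size?** For each true loss, the binomial probabilities of all pairs of results with a non-significant uncorrected chi-square (two-sided 5%) were summed, with n = 132 per group and pB = 0.645.

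| True loss in Group A (points) | Chance of P > 0.05 |
|---|---|
| 3.3 | 92% |
| 5 | 87% |
| 8 | 73% |
| 10 | 61% |
| 12 | 48% |
| 13 | 42% |
| 15 | 29% |
| 20 | 9% |

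With Yates' correction, the figures are 66% at 10 points and 53% at 12. With 126 per group (280 × 0.90 = 252), the uncorrected test gives 64% at 10 points, 52% at 12 and 33% at 15. A 10-point loss is 10/64.5 = 15.5% of the 12+3-core yield, about one in six.

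**4. Largest non-significant deficit.** With 85/132 (64.4%) in Group B, 70/132 (53.0%) in Group A is 11.4 points lower. The pooled rate is 155/264 = 0.587, the standard error √(0.587 × 0.413 × 2/132) = 0.0606, and z = 0.1136/0.0606 = 1.88, so P > 0.05. The simple 95% interval for the loss runs from −0.4 to 23.2 points. The result is not significant, yet it does not exclude a loss of more than 20 points.

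At an assumed 20-point margin, non-inferiority would need an observed loss below about 20 − 1.96 × 5.94 = 8.4 points. Observed losses between that and 11.4 points would be non-significant on the stated test and would still fail non-inferiority.

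**The case against.** Section 2.6 is a generic sentence in a condensed article, and a fuller protocol or SAP may hold the margin and the decision rule. Their absence here is therefore no finding. That stands, and the point does not rest on it. It rests on what the article does state: a test of difference and a two-sided rule applied to every result. A non-inferiority SAP would have to override that text rather than complete it.

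Four stronger readings are tempting, and the document does not support them.

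- *The trial is declared as non-inferiority.* It is not. Neither the term nor a margin appears. The reading is inferred from the aim, the lower expected rate in Group A and the arithmetic.
- *One-sided 2.5% in section 2.5 contradicts two-sided 5% in section 2.6.* The levels do not conflict: one limit of a two-sided 95% interval is a one-sided 2.5% bound. The mismatch lies in the hypothesis tested.
- *The investigators will take P > 0.05 as support for 6 cores.* No text says so. The aim is worded as finding out whether, and the Discussion calls the findings preliminary. The risk follows only from there being no other stated criterion.
- *A large loss would usually be missed.* With the uncorrected test at 132 per group, a non-significant result is more likely than not at 10 points (61%), but not at 12 (48%), and it is uncommon at 20 (9%).

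**Conclusion.** The concern holds in this limited form. The one between-group test stated for the primary outcome cannot deliver the conclusion the trial seeks, and it is not the test that 132 per group can serve. As a test of difference, the planned size has about 8% power for the stated rates and falls short by a factor of about 25 (3,365/132).

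The practical size depends on the true loss. The stated test would be non-significant in about three of five trials at a 10-point loss, under a third at 15 points and about one in eleven at 20. These figures assume 64.5% detection in Group B, 132 analysed men per group and the uncorrected chi-square. The 20-point margin is a back-calculation, not a figure in the protocol.

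This should be corrected before results by arm are known, because the main conclusion depends on it and a margin chosen afterwards would carry little weight.

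**What to change.** - **Section 2.6:** make the primary analysis the risk difference in detection (A minus B) with a two-sided 95% confidence interval, for example Newcombe or Miettinen–Nurminen. Apply it to PCa detection, the outcome that was sized, and report csPCa in the same way.
- **Section 2.5:** name the hypothesis and state the margin actually used to obtain 132.
- **Decision rule:** conclude non-inferiority only if the lower confidence limit lies above minus that margin, and state that a non-significant chi-square will not be read as equivalence.

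**Cost.** This takes a few sentences and no new data, provided the margin behind 132 is kept. The downside is that this margin is wide, at about 20 points if the stated rates were used as stated. A narrower one would leave 132 per group with only about 50% power at 15 points and 20% at 10, or would need 268 or 816 per group for 80%. The protocol should say this openly.

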## Discussion

3.

Nowadays, it is strongly recommended that for biopsy naïve men with PIRADS score >2, combining TBx and SBx is needed. However, how to identify an ideal arrangement or permutation for systematic and TBx remains a challenge for clinicians. In other words, an ideal biopsy strategy should be developed with the goal of minimizing procedure invasion, having fewer biopsy-related complications, and maximizing the detection rate of csPCa and minimizing the detection rate of clinically insignificant cancers.

The development of systematic prostate biopsies has revolutionized over the past few decades. In 1989, Hodge et al. originally described the scheme of transrectal ultrasound guidance systematic sextant biopsies to detect prostate cancer (12); However, it could miss up to 30% of PCa (13). Then, a prospective study reported that the detection rate of PCa raised 16% when combining sextant and lateral biopsies (10 cores peripheral zone biopsies) compared to the routine sextant biopsies (194/202, 96% vs. 161/202, 80%) (14). Followed by, a 10-core biopsy scheme was developed by Gore et al. who revealed the detection rate of PCa between 10-core scheme (except for 2 mid cores from standard sextant scheme) and 12-core regional biopsy was equivalent (15). Importantly, considering the inadequacy of standard sextant biopsies, a multi-practice community based study emphasized the necessity for extended lateral side of the peripheral zone sampling (16). Therefore, in the era of SBx, the optimal sampling scheme for biopsy-naïve patients reached the consensus of a 10- to 12-cores.

With the development of mpMRI, TBx is widely accepted and related to detecting more csPCa compared to SBx. Currently, various protocols of MEI ultrasound fusion TBx were reported with 1 to 9 cores per lesion (17, 18). A consensus by the American Urological Association and Society of Abdominal Radiology guideline recommended that more than 2 cores per lesion is required for PCa detection (19). Additionally, the PRECISION trial showed that 4 cores per target to suspicious MRI lesions performed better than a standard 10- to 12-core SBx (5). More recently, Song et al. conducted a prospective trial and concluded that 3 cores per targeted lesion were suitable for transperineal MRI ultrasound fusion biopsy (20). Our previous research also proved that 3 cores per target might be the optimal biopsy scheme of MRI -targeted prostate biopsy (8).

Although targeted biopsy alone using far less biopsy cores detected no less Gleason ≥3 + 4 and fewer Gleason 6 cancers when compared with SBx, it may still inevitably underestimate a proportion of high-grade PCa in comparison with the combined approach (5, 6, 21). Previous study indicated that when using a combined SBx and targeted biopsy as a reference, directly omitting SBx resulted in detecting 13% less csPCa (7). Therefore, as strongly recommended by EAU guideline, combining targeted biopsy and SBx remains the optimal choice currently (2, 22). As previously reported, the suitable cores for the targeted and SBx have been separately investigated. Notably, how to keep the total cores (SBx plus target biopsy) lower while optimize the detection rate of csPCa is another urgent problem in the era of combined biopsy.

To optimize the sampling scheme of the combined prostate biopsy, the protocols of how to reduce biopsy cores were experimentally explored. Liu et al. divided the prostate into left, right, transitional zone, and peripheral zone, and they prospectively detected that targeted biopsy plus fewer SBx cores (nontargeted sector) had an equal PCa and csPCa detection rate as compared with the standard targeted biopsy + SBx (four cores less per patient) (23). In addition, Kachanov et al. showed that a peripheral targeted biopsy plus SBx without any transitional zone sampling detected the similar csPCa detection rate compared with the standard extended protocol (24). Furthermore, Freifeld et al. demonstrated that targeted biopsy + ipsilateral SBx may increase the detection rate of csPCa compared with only targeted biopsy, while limiting overdiagnosis of indolent PCa when comparing with targeted biopsy + contralateral SBx (25). Meanwhile, Aminsharifi et al. proposed a Reduced Core Targeted biopsy template (image—targeted + laterally directed sextant biopsy) and found that targeted biopsy + sextant biopsy could detect more csPCa patients compared to sextant biopsy; however, they did not compare the diagnostic efficiency of this sampling scheme with that of targeted biopsy + 12-core SBx (26). Shen et al. further demonstrated that targeted biopsy + lateral 6-core SBx showed the same diagnostic performance as that of targeted biopsy + 12-core SBx but with reduced cores in men with suspected PCa (27). Hence, prospective studies are warranted to provide a higher level of evidence for the optimal sampling scheme in biopsy naïve men with a PIRADS score of >2. Especially, the recent EAU guideline strongly recommended transperineal route as the preferred method considering the lower infection rates and better coverage of the anterior zone, compared to transrectal procedures (2, 22). This study is the first RCT to evaluate whether a 3-core MRI-targeted plus 6-core SBx could be considered as the optimal sampling scheme in the setting of transperineal route under local anesthesia.

There are some limitations in this study. Firstly, this trial is performed in one single high-volume center. However, we believe our preliminary findings will go a step further in providing a higher level of evidence for the optimal sampling scheme in the era of combined prostate biopsy. Secondly, the cognitive fusion mpMRI-targeted biopsies rather than ultrasound/MRI fusion software or direct in-bore guidance biopsy are performed in our institution. Nevertheless, current literatures do not report a clear superiority in detecting csPCa among these three different approaches (2), Wegelin et al. who conducted a systematic review and meta-analysis reported that no significant advantage was found between in-bore MRI target biopsy, MRI-transrectal ultrasound fusion, and cognitive registration in detecting PCa and csPCa (28). Then, Watts et al. also showed that no significant difference of PCa detection rate between MRI-ultrasound image guided fusion biopsy and cognitive biopsy (29). Thirdly, the final pathological diagnosis in both groups was based on biopsy rather than radical prostatectomy specimens which may cause potential bias. Notably, patients with negative biopsy are not likely to undergo radical therapy in clinical practice, and regular follow up after negative biopsy are also routinely scheduled in our center. Finally, we could not explore the racial disparities in our included population due to the single-center study design.

